
## 8.2 Secondary Outcomes - Implementation

### Reach (proportion of patients)

Secondary reach outcomes will be measured as the proportion of patients enrolled in the patient cPRO portal among those eligible and the proportion of patients who are referred for appropriate services from among those that trigger an alert in cPRO. Similar to the primary reach outcome, these proportions will be defined at the clinic level for each 1-month period. The analytic framework for these clinic-level outcomes will be the same as what is described for the primary reach outcome (Section 8.1).

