**Pre-Implementation Phase:**

As part of NM oncology standard of care, NMPRO system sends out the “*Your Pre-appointment Symptom and Needs Assessment (cPRO-Monitor)*” questionnaire to patients 72 hours prior scheduled oncology visit via MyChart. At the start of the study, the NMPRO Symptom and Needs Assessment questionnaire originally consisted of PROMIS Depression, Anxiety, Fatigue, Pain Interference and Physical Function CATs, along with a supportive care checklist in which patients endorse any supportive care needs for which they want to be contacted by a health care provider. However, as part of an ongoing QI initiative to implement and evaluate NMPRO in parallel to this protocol, workflow limitations that were encountered after we began implementation required that we shorten the PROMIS assessments to just two items per symptom domain. The two-item short forms are comprised of a subset of items from the longer, already-approved CAT approach. If the patient does not complete the NMPRO Symptom and Needs Assessment questionnaire prior to scheduled oncology visit, they will have the option to complete the NMPRO Symptom and Needs Assessment in clinic. NMRPRO alerts generated by elevated scores on the Symptom and Needs Assessment questionnaire are responded by social work (for anxiety, depression or practical needs) or the medical team (for fatigue and physical function) or dietitian (for nutritional needs) within 72 hours. Participants are clearly instructed that in case of an emergency or the need for immediate care, patients should call 911, visit the ER or the urgent oncology care clinics.

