#### Primary implementation outcome in NU IMPACT:

- Patient-level adoption measured by the proportion of patients completing cPRO among those eligible for cPRO

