#### Secondary implementation outcomes in NU IMPACT:

- Patient-level reach measured by the proportion of patients enrolled in cPRO among those eligible for cPRO
- Patient-level reach measured by the proportion of patients who are referred for appropriate services from among those that trigger an alert in cPRO
- Provider-level adoption measured by the proportion of unique clinicians who use a cPRO dot phrase to follow up on triggers received from patients
- Survey outcomes evaluating appropriateness, acceptability, feasibility, and sustainability of the implementation strategies package supporting cPRO
- Qualitative data from focus group interviews concerning barriers/facilitators, acceptability, feasibility, and sustainability

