## 5.0 STUDY HYPOTHESES

The primary implementation hypothesis is that the system-level multicomponent package of implementation strategies for oncology symptom assessment and management at NMHC will increase the cluster-level reach rate of cPRO to eligible patients. The primary effectiveness hypothesis is that cancer patients at NMHC who are randomized to EC will have better PRO outcomes over time compared to cancer patients at NMHC who are randomized to UC.

Secondary implementation hypotheses are that the system-level multicomponent package of implementation strategies for oncology symptom assessment and management at NMHC will increase adoption of cPRO at the provider level as evidenced by referrals for appropriate services when a patient triggers in cPRO and the reach rate of patients enrolling in the portal. It is also hypothesized that system-level strategies will be appropriate, acceptable, feasible, and sustainable. Secondary effectiveness hypotheses are that cancer patients at NMHC who are randomized to EC will have lower healthcare utilization, better cancer treatment delivery, better cancer treatment satisfaction, better health related quality of life, better self-management, lower toxicity, better physical health and lower financial burden compared to cancer patients at NMHC who are randomized to UC.

The exploratory hypothesis is that cancer patients randomized to EC will have better clinical outcomes compared to cancer patients randomized to UC.

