## 8.0 STATISTICAL ANALYSES - IMPLEMENTATION

### 8.1 Primary Outcome - Implementation

#### Reach (proportion of patients)

Reach will be measured by the proportion of patients completing one or more ( $\geq 1$ ) cPRO assessments among those eligible for cPRO. This analysis will be a clinic-level analysis analyzed under a cross-sectional design and will only include clinics in the 6 clusters that were randomized. We will calculate reach using 1-month sampling periods within each clinic (as less than 100 individuals in a clinic would be too small for a per-month analysis, our back up will be a 2-month sampling period rather than a 1-month sampling period). The outcome variable will be defined as the proportion of participants who complete a cPRO assessment among those who are eligible within the clinic and the 1-month period. Thus, each month and clinic will have a single data point expressed as a proportion of eligible individuals reached. There are approximately 30 clinics (median of 5 clinics per cluster) and 42 monthly reach proportions will be calculated for each clinic; thus we anticipate 1260 data points for the primary outcome variable. We will use the nlme package in R to perform generalized least squares linear regression modeling with an exposure indicator variable for post-I v. pre-I [referent] entry into the study as the primary predictor of interest. An autoregressive structure will be specified for the correlation structure among the linear model residuals resulting from the repeated measurements of reach within clinic; a lag 1 model will be specified, but model fit under this and other correlation structure specifications will be evaluated according to AIC and BIC. In the generalized least squares setting, the within-clinic repeated measures observation structure is used to define the structure of the covariance matrix. The degrees of freedom is thus the number of calculated proportions calculated for all 1-month intervals and all clinics, less the number of model parameters, including those specified in the covariance matrix. We will perform analyses using an identity link for the outcome variable to estimate risk differences on the raw proportions. In addition, we will log-transform the outcomes to estimate relative risk ratios. We will use clinic-level covariate adjustment for: 1) cluster; 2) time (categorical variable for quarter); 3) number of 1.0 FTE equivalent oncologists per clinic; 4) number of unique patients per clinic; and 5) type of cancer care clinic (e.g., medical oncology, surgical oncology). In sensitivity analyses, we will use weights in the generalized least squares model based on the number of unique eligible patients per clinic. Restricted maximum likelihood (REML) will be used for model parameter estimation as it produces unbiased estimates of the variance and covariance parameters. The primary predictor of interest will be post-I v. pre-I entry into the study, i.e. whether the individual became eligible for cPRO during the pre-I or post-I phase at their site. This clinic-level analysis was chosen as we hypothesize that the impact of the implementation strategy will vary by clinic due to clinic size (clinicians and patients). We will also test for cluster\*treatment and time\*treatment effects to test for a lagged/delayed effect of the exposure, and clinic effects within clusters, in the overall model. Rather than including an a priori transition period, we will conduct a sensitivity analysis around the crossover point in two 1-month increments.

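### Referral reach is compared post-I v. pre-I only among alerted patients, a group that rising cPRO completion can reshape, so on its own it should not be read as a change in provider practice

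*Combined protocol and SAP*

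**What the plan says.** - **Outcome.** SAP Section 8.2 defines one secondary reach outcome as the "proportion of patients who are referred for appropriate services from among those that trigger an alert in cPRO", for each clinic and 1-month period. SAP Section 2.0 lists the same ratio as patient-level reach.
- **Entry to the denominator.** Protocol Section 8.0 (Pre-Implementation Phase) describes "alerts generated by elevated scores on the Symptom and Needs Assessment questionnaire". A patient who does not complete the questionnaire cannot be counted.
- **Target of the package.** SAP Section 2.0 gives the primary implementation outcome as "Patient-level adoption measured by the proportion of patients completing cPRO among those eligible for cPRO". SAP Section 5.0 hypothesises that the package "will increase the cluster-level reach rate of cPRO to eligible patients".
- **Model.** Section 8.2 takes over the framework of Section 8.1: "This analysis will be a clinic-level analysis analyzed under a cross-sectional design", with a post-I v. pre-I indicator. The covariates are cluster, quarter, oncologist FTE, number of unique patients and clinic type. All describe the clinic; none describes the alerted patients.
- **Interpretation.** SAP Section 5.0 hypothesises higher provider-level adoption, "as evidenced by referrals for appropriate services when a patient triggers in cPRO".
- **Related plans.** SAP Section 7.2 compares patient characteristics on each implementation outcome by phase, descriptively. No adjustment or sensitivity analysis follows from it, and alert domain and severity are not on its list. No outcome counts referrals among all eligible patients.

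**The concern.** The random order of roll-out supports comparisons among eligible patients. It does not support a comparison within a subset that the exposure helps to form. If the package works as hypothesised, more patients complete cPRO and more enter the alert denominator. When those extra patients have a different chance of referral from patients who would have completed anyway, the proportion changes although no clinician has changed what they do for any type of patient.

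The documents give one route by which chances could differ. Protocol Section 8.0 sends alerts to social work, the medical team or a dietitian according to domain. A change in the mix of alert domains could then move the pooled proportion with each responder's behaviour constant.

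At stake is the statement in SAP Section 5.0. A successful package could appear to worsen referral, or a composition gain could be credited to providers.

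**Working it through.** The documents give no completion, alert or referral rate for this outcome and no power statement, so there is no figure to reproduce. Every rate below is an assumption chosen to show the mechanism.

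**Illustration 1.** Per 100 eligible patients, completion rises from 30 to 50. The original 30 still complete. The alert rate among completers is 30% throughout. Original completers are referred after 50% of alerts, newly reached patients with probability r. Neither changes between phases.

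- Planned proportion, pre-I: 50%.
- Planned proportion, post-I: (30 × 0.5 + 20 × r)/50. The shift is therefore 0.4 × (r - 0.5).
- Referrals per 100 eligible: completers × 0.3 × planned proportion. Pre-I this is 30 × 0.3 × 0.5 = 4.5.

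| r | Planned proportion post-I | Shift (points) | Referrals per 100 eligible post-I |
|---|---|---|---|
| 0.3 | (15 + 6)/50 = 42% | -8 | 50 × 0.3 × 0.42 = 6.3 |
| 0.4 | (15 + 8)/50 = 46% | -4 | 50 × 0.3 × 0.46 = 6.9 |
| 0.5 | (15 + 10)/50 = 50% | 0 | 50 × 0.3 × 0.50 = 7.5 |
| 0.6 | (15 + 12)/50 = 54% | +4 | 50 × 0.3 × 0.54 = 8.1 |

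With a smaller rise, 30 to 40, newly reached patients are 10/40 = 0.25 of completers. The shift is then 0.25 × (r - 0.5): -5 points at r = 0.3 and +2.5 at r = 0.6.

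**Illustration 2.** Two equally common patient types, alert rate 30% in both, fixed referral chances. Completion rises from 40% to 50% in type A and from 10% to 40% in type B, so overall from 25% to 45%.

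- Referral 0.6 in A, 0.3 in B. Pre-I: (0.060 × 0.6 + 0.015 × 0.3)/0.075 = 54.0%. Post-I: (0.075 × 0.6 + 0.060 × 0.3)/0.135 = 46.7%. Shift -7.3 points.
- Chances reversed: 36.0% to 43.3%, shift +7.3.
- Milder case (completion 40% to 45% in A, 10% to 25% in B; referral 0.5 and 0.4): 48.0% to 46.4%, shift -1.6.
- Equal referral chances, or completion doubling in both types: shift 0.

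**Does the planned adjustment remove it?** The layout was simulated with 30 clinics, 6 randomised clusters and 42 months, using cluster and quarter terms, least squares with independent residuals, an assumed 100 eligible patients per clinic-month, and 500 runs. Referral behaviour per alert was held fixed.

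| Case from illustration 2 | Mean post-I coefficient | Nominally significant, two-sided 5% |
|---|---|---|
| Referral 0.6 / 0.3 | -0.075 | 96% of runs |
| Referral 0.3 / 0.6 | +0.074 | 96% of runs |
| Milder case | -0.015 | 12% of runs |
| Equal chances | -0.001 | 7% of runs |

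Cluster and quarter terms leave the shift in place. The other Section 8.1 covariates were not simulated, but they are also clinic-level and carry no information on who is alerted. Only the possibility and direction of the shift should be taken from these runs. The rejection rates depend on the assumed inputs.

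**The case against.** The alert-based denominator is deliberate. Protocol Section 8.0 (Evaluation of Implementation) defines it as the second level of penetration and ties it to fidelity, with near-complete follow-up of triggers as the standard. Against that standard a fall from 50% to 42% is a true finding, since a smaller share of alerts is acted on. Much of the context is also planned. Completion is the primary outcome, the EHR reports cover alert counts and time to response, SAP Section 7.2 describes patients by phase, and Section 8.2 has a separate outcome with clinicians as denominator. Finally, the bias is conditional: higher completion alone does not make the alerted groups differ in their chance of referral.

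All of this stands, and it limits the point. It does not remove it, because SAP Section 5.0 takes referral per trigger as evidence of provider adoption and none of the planned context enters the model. The clinician-based outcome also depends on alerted patients.

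A reader might go further and infer that referrals per eligible patient should replace the planned proportion. The documents do not support that. Section 5.0 asks about response per alert, and the per-eligible measure rises with completion alone, as every row of the first table shows. It can even hide deterioration. With completion rising from 30% to 50% and an alert rate of 30%, referral of every alerted patient could fall from 50% to 31% and the measure would still rise, from 4.5 to 50 × 0.3 × 0.31 = 4.65 per 100.

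**Conclusion.** The point holds in a limited form. The alert-based contrast is conditioned on a group formed after exposure, through the completion that the package is meant to raise, and the planned covariates cannot correct for its composition. Under the assumed rates the proportion moves by about -8 to +4 points with referral practice unchanged. A smaller rise in completion or closer referral chances gives less, and equal chances give zero.

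This rests on two things the documents do not establish: that completion rises, which is the trial's hypothesis, and that newly reached alerted patients differ in their chance of referral, in a direction that is unknown. A reader might infer that the planned comparison is necessarily biased or that the proportion is invalid. Neither follows. It remains a sound process measure of follow-up per alert. What lacks support is reading its pre/post change, by itself, as a change in provider adoption. This is an optional improvement to one secondary outcome and does not touch the primary analyses.

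**What to change.** 1. Keep the alert-based proportion in SAP Section 8.2 and label it a process measure of follow-up per alert.
2. Add a companion outcome in the same clinic-level model: patients alerted and referred, divided by eligible patients, per clinic and month. Read it as the package's overall effect on referrals, a comparison the roll-out order supports, and not as provider behaviour.
3. Report completion among eligible patients and alert rate among completers, by phase, beside both.
4. Qualify SAP Section 5.0: the alert-based contrast counts as evidence on provider adoption only if it holds after adjustment or standardisation for alert domain, severity and patient mix. Protocol Section 19.0, Table 4, lists cPRO scores for five domains. Alerts arising from the needs checklist would have to be classified from the planned alert queries.
5. While editing, reconcile the sampling period for this proportion, which is 3 months in Protocol Section 8.0 and 1 month in SAP Section 8.2.

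**Cost.** One or two extra model runs. The companion's numerator and denominator are already needed for planned outcomes, and SAP Section 1.0 says SAP changes need no protocol amendment. The downside is that the companion mixes patient completion with provider response, so it has to stand beside the planned proportion and cannot replace it.

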### Adoption (provider-level)

Adoption by providers will be measured by the proportion of clinicians within a clinic who refer  $\geq 1$  patient who trigger an alert for services, using a cPRO dot phrase, within each 1-month period. The analytic framework for these clinic-level outcomes will be the same as what is described for the primary reach outcome, but with the proportion outcome defined at the provider level (Section 8.1). We will perform a cluster-level analysis if there are fewer than 20 clinicians in any one clinic.

## Survey Outcomes for Appropriateness, Acceptability, Feasibility, and Sustainability

Survey summary scores will be computed according to established methods in the literature concerning full/subscale scores, the metric reported, etc. We will examine score differences between respondents by provider/respondent type, associated cluster, and the other clinician covariates previously specified.

## 9.0 STATISTICAL ANALYSES - EFFECTIVENESS

### 9.1 Primary Outcomes - Effectiveness

#### PROs

Using each of the separate PROMIS domain status scores (i.e., Anxiety, Depression, Fatigue, Pain Interference, and Physical Function) collected at baseline and at regular monthly intervals, primary analyses will use longitudinal models to estimate the time-averaged difference in PROs across groups. Primary effectiveness estimates will be based on post-I data with a comparison of longitudinal PROs for patients randomized to Post-I EC v. Post-I UC. Linear mixed models will be used for these analyses with a fixed effect for treatment arm (Post-I EC v. Post-I UC) as the primary predictor of interest and fixed effects for model adjustments for cluster, cancer continuum, gender, language preference, baseline PRO value and time of enrollment (categorical variable for quarter enrolled). Individual-level random effects with an autoregressive covariance structure will be included in the mixed models to account for dependence of within-individual PRO measurements over time. Multiple comparisons adjustment for the five primary tests of hypothesis will be performed using the step-down Dunnett procedure. For reporting purposes, confidence intervals for treatment effects for the five primary outcomes will be reported with lower and upper bounds simultaneously estimated to correspond with Dunnett correction. Sensitivity of model estimates and statistical inference under unstructured and compound symmetry covariance structures will be explored. In addition to the overall time-averaged difference, we will also report estimated differences from baseline at specific monthly timepoints.

Secondary analyses will also examine changes from baseline to the 12-month follow-up time point as well as change from baseline to the other monthly follow-up time points using the directly observed differences from baseline at these timepoints. Linear regression will be used for these analyses with treatment arm (Post-I EC v. Post-I UC) as the primary predictor of interest and model adjustments for cluster, cancer continuum, gender, language preference, baseline PRO value and time of enrollment (categorical variable for quarter enrolled). These effect estimates will be compared to effect estimates at each time point calculated in the primary analysis model that uses all longitudinal measurements.

Recognizing the possibility of contamination effects for the treatment arms during the post-I period, we will augment the primary analyses to include longitudinal PRO data from the Pre-I period. Linear mixed models will be used as described for the primary analyses but extending the primary predictor of interest to a multicategory variable (Post-I EC, Post-I UC, Pre-I). Adjustments for cluster, cancer continuum, gender, language preference, baseline PRO value and time of enrollment, and the individual-level random effects, will be included as described above. The Post-I UC cohort will be treated as the referent group to facilitate formal primary comparison with outcomes for the Post-I EC group, and to gauge comparability of outcomes for Post-I UC and Pre-I patients. This approach will also allow for a contrast test between Post-I EC and Pre-I. If longitudinal PROs for Post-I UC and Pre-I are not significantly different, and if the effectiveness estimate for Post-I EC v. Pre-I is similar to the primary Post-I EC v. Post-I UC comparison, this will suggest lack of contamination. If longitudinal PRO differences for Post-I UC v. Pre-I are significantly different and/or the effectiveness estimate for Post-I EC v. Pre-I is different from the primary Post-I EC v. Post-I UC comparison, this may suggest some level of treatment arm contamination during the Post-I phase. This latter scenario may also be indicative of system-level implementation effects and will need to be interpreted in the context of implementation analysis findings.

Multiple imputation using chained equations will be used for missing data under a range of scenarios from missing at random to informative missingness. Sensitivity of parameter estimates to these assumptions will be evaluated.

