### **15.0 Risks to Participants:**

This project presents minimal risk to participants in receiving the enhanced care (EC) intervention, completing self-report measures or participating in focus groups (or individual interviews). In the over 3,000 patients assessed through our prior pilot work, there have been no reported incidents of distress or other adverse events. Additionally, Northwestern University's Department of Medical Social Sciences has not encountered severe distress in the thousands of cancer patients and survivors who have completed self-report symptom assessments or focus groups / qualitative

interviews in previous studies. Of the more than hundreds of thousands of participants over 15 years, less than 1% have become emotionally upset to any extent. Lastly, as in any research, there is a slight risk of loss of confidentiality. Measures taken in these rare instances are described below. Participants randomized to the EC condition will receive information (e.g., tools, modules, skills) specific to improving self-management skills, gaining knowledge regarding their medical condition, improving communication skills and empowering them to improve motivation and self-management. In rare cases, a participant may feel overwhelmed by such information and experience transitory distress states. However, this has not been our experience in multiple web-based studies that the study team has conducted. Nonetheless, regardless of study cohort or intervention arm, participants are instructed to call study staff with any concerns or questions they may have.

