Summary data reports will not contain any identifying information. Upon completion of the study and data retention period, patient identifiers will be deleted in compliance with the Health Insurance Portability and Accountability Act. Though we regard the risks of participating in this study as very low, we will take care that every recruiter, project personnel, etc. is trained to handle situations sensitively and with empathy. All research staff are required to complete NU mandated training on the Protection of Human Research Participants, and this training experience must be renewed on a yearly basis. Certificates for all research staff will be kept on file in the PI's office at each respective site. As risks are relatively low and easily managed, and because benefits for participants are potentially substantial, the balance of risks-to-benefits are reasonable. Despite extremely low incidence in related prior studies, it is conceivable that a participant may later become severely depressed or otherwise distressed while on study. Therefore, as we have in prior studies, participants who report significant distress (in their assessment measures or communications with study staff) will be referred to the cancer clinics' Supportive Oncology Program. Drs. [name], [name], and [name] (both clinical psychologists) will ensure that study staff are trained to monitor for significant patient emotional distress or physical symptoms that merit referral (and how to make those referrals). Study staff will be instructed on the appropriate courses of referral if a participant is considered to be at risk for a safety concern (using the existing Supportive Oncology Crisis Protocol available at each clinic). Telephone and pager numbers for members of the Supportive Oncology Team as well as how to contact on-call oncology providers will be kept on file to be used in the event of any mental or physical health emergencies. Our study

team ([name], [name], [name], [name]) also has crisis intervention training and, if warranted, can assist with clinical assessment (e.g., suicidal ideation, plan of action, and likelihood of carrying out the plan).

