experienced cancer biostatistician with the primary research focus in the design and analysis of clinical trials. [name] is also Director of the Quantitative Data Sciences Core at the Robert H. Lurie Comprehensive Cancer Center at Northwestern University, a shared resource that provides support to cancer researchers in the areas of biostatistics, bioinformatics and clinical informatics. The DSMB will also include [name], Professor (Radiology), Division of Abdominal Radiology, Michigan Medicine. [name] is the Assistant Chair for Clinical Research at the University of Michigan and has expertise in multi-disciplinary, multi-center clinical trials on prevention, surveillance and cancer care delivery. The final member is [name], Professor (Health Policy and Management), UNC-Chapel Hill. [name] is a licensed clinical health psychologist with expertise in psychosocial oncology and measuring patient-centered outcomes in oncology. None of these DSMB members are associated with the proposed work and all have DSMB experience. The DSMB will meet semi-annually via WebEx, beginning in the fourth quarter of year 1. Occurrence of unexpected serious adverse events (e.g., hospitalization, injury, or death of a study participant) will be discussed at weekly project meetings. Adverse events will be documented, logged and (those meeting the criteria of 'Reportable New Information') submitted to the NU-IRB in writing as mandated. The PI will review data safety quarterly, and a cumulative report will be submitted on an annual basis as required for continuing review and/or final report. Interim study analyses for the purpose of discontinuing the randomized arm of the study will only be conducted if during a review of adverse events it seems that risks or complications appear to be greater than those originally stated. If the PI suspects that an unusual number of adverse events is occurring, our Statistician, [name], in consultation with [name], will break the condition assignment and participant identifier code and determine if the adverse events occur significantly more frequently in any one condition. The DSMB will be convened at this point (in addition to biannual meetings) to address unexpected complications. As the potential source of adverse events is likely to come from psychosocial assessment, or the self-management intervention, our statistician will attempt to assess any relationship between these factors and adverse events. In the unlikely event of such analyses, the IRB will be kept informed of the results in a timely manner. Moreover, the IRB will be notified within one working day of any temporary or permanent suspension of the study protocol. Adherence to the protocol as well as data accuracy and security are detailed in the protocol and informed consent document. No study personnel or members of the DSMB have a conflict of interest with the study protocol.

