## NU IMPACT Statistical Analysis Plan

### 1.0 INTRODUCTION

This Statistical Analysis Plan (SAP) for the Northwestern University IMPACT Research Center (NU IMPACT) study includes all plans for data summary and statistical analyses in support of NU IMPACT primary, secondary and exploratory hypotheses. A summary analysis plan and sample size justification are included in the NU IMPACT Protocol. The SAP is intended to provide a more detailed description of planned analyses. The SAP is not considered part of the protocol. Thus, modifications to the SAP do not require protocol amendments.

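### The SAP plans no by-arm count of distress, the harm the protocol names for Enhanced Care, and the protocol compares adverse events by arm only if an excess is suspected

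*Combined protocol and SAP*

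**What the plan says.** **Harm.** Protocol 15.0 says of the EC material: "In rare cases, a participant may feel overwhelmed by such information and experience transitory distress states". It adds that the team has not seen this in its earlier web-based studies. The other risk it names applies to every participant: "as in any research, there is a slight risk of loss of confidentiality". The only rate it gives is "less than 1% have become emotionally upset to any extent", from earlier self-report assessments, focus groups and interviews, not from EC.

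**Safety monitoring.** Under Protocol 17.0, adverse events are documented and logged, the principal investigator reviews safety quarterly, and the DSMB meets semi-annually. The self-management intervention is named as one of two likely sources of adverse events. If the principal investigator suspects an unusual number, the statistician breaks the code to "determine if the adverse events occur significantly more frequently in any one condition". The examples of unexpected serious events are hospitalization, injury and death. Distress is not defined as an adverse event.

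**Response to distress.** Protocol 16.0: "participants who report significant distress (in their assessment measures or communications with study staff) will be referred" to the Supportive Oncology Program, with a Crisis Protocol available at each clinic.

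**Analysis.** SAP 9.1 states that "primary analyses will use longitudinal models to estimate the time-averaged difference in PROs across groups" and that "we will also report estimated differences from baseline at specific monthly timepoints". Its secondary regressions on change from baseline also compare means. SAP 9.2 summarises supportive care visits by arm with means and five-number summaries, then adds them into one utilization score. SAP 7.1 limits the effectiveness data set to patients with a baseline PRO and at least one later PRO. Neither the outcome lists in SAP 2.0 nor the analyses in SAP 8 and 9 include an adverse-event table, a count of distress referrals or a measure of individual worsening.

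**The concern.** A mean difference answers whether patients on average do better on EC. It does not answer whether a few are made worse for a short time, because benefit in most patients offsets harm in a few, and averaging over 12 months dilutes a one-month event further. The analysis that would address that question, a comparison of events by condition, depends on someone first noticing an excess. The excess that matters is a difference between arms, whereas suspicion as Protocol 17.0 describes it comes before the code is broken and so rests largely on the overall number.

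At stake is the reporting of harm. The trial could report EC as beneficial or neutral on Anxiety and Depression, and as minimal risk, with no planned look by arm at the harm the protocol foresaw. The primary efficacy inference is not affected.

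**Working it through.** **1. Reproduce the SAP's sample size.** Inputs from SAP 6.0: difference 0.3 SD, alpha 0.01 (taken as two-sided), power 90%, correlation 0.5 with compound symmetry. SAP 2.0 gives 12 monthly follow-up measurements.
- Variance of a patient's 12-month mean, in SD² units: (1 + 11 × 0.5)/12 = 0.5417.
- Per arm: 2 × (2.576 + 1.282)² × 0.5417/0.3² = 179.1, so 180 per arm and 360 in total, as stated.
- 360/(1 − 0.64) = 1000, as stated.

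**2. Standard errors at 500 per arm.**
- Time-averaged: √(2 × 0.5417/500) = 0.047 SD.
- Single month: √(2/500) = 0.063 SD.
- At 180 per arm these rise to 0.078 and 0.105 SD.

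**3. What the harm does to a mean.** The documents give no EC distress rate, size or duration. Assume a share p of 0.5% to 2% worsens by D of 1 to 2 SD for one month.
- Time-averaged shift = p × D/12: from 0.005 × 1/12 = 0.0004 SD to 0.02 × 2/12 = 0.0033 SD. The chance of significance at 0.01 is 0.0100 to 0.0102, in effect the type I error rate.
- Single-month shift, if every case falls in the same month, = p × D: 0.005 to 0.04 SD. Power is 0.010 to 0.027 at alpha 0.01 and 0.051 to 0.097 at alpha 0.05.
- Baseline adjustment in SAP 9.1 helps little. At correlation 0.5 it removes 0.5² = 0.25 of the variance, giving a time-averaged SE of √(2 × 0.2917/500) = 0.034 SD, still about ten times the largest shift.

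**4. What a count shows.** If every case is recorded, the chance of at least one in 500 EC patients is 1 − (1 − p)^500: 0.92 at 0.5%, 0.993 at 1% and above 0.999 at 2%.

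**5. What the conditional trigger can miss.** Illustrative counts, EC v. UC, 500 per arm:

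| EC v. UC | Pooled rate | Fisher exact p |
|---|---|---|
| 5 v. 0 | 5/1000 = 0.5% | 0.06 |
| 8 v. 0 | 8/1000 = 0.8% | 0.008 |
| 15 v. 5 | 20/1000 = 2.0% | 0.039 |

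The first two pooled rates lie below the only figure in Protocol 15.0 (under 1%), so nothing in the total would look unusual. For 15 v. 5 the risk difference is 3.0% − 1.0% = 2.0 points. Its SE is √(0.03 × 0.97/500 + 0.01 × 0.99/500) = 0.88 points, giving a 95% CI of 0.3 to 3.7.

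A formal test of such counts is weak. At true rates of 1% and 3%, Fisher power is about 56%.

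**6. Would a cut on the PROMIS score do the job?** Simulation with an assumed mean of 50, SD 10, 500 per arm, and 2% of EC patients raised 10 points in one month. The outcome is crossing a cut at any of 12 surveys, among patients below it at baseline. The cuts are also assumed.

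| Correlation, cut | UC | EC | 95% CI half-width |
|---|---|---|---|
| 0.5, 60 | 50.6% | 50.8% | 6.8 points |
| 0.5, 65 | 29.7% | 29.9% | 5.9 points |
| 0.8, 65 | 15.2% | 15.5% | 4.6 points |

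Ordinary fluctuation swamps the assumed harm.

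**The case against.** **Protocol 17.0 already provides a harms route.** It logs events, names the self-management intervention as a likely source, and has the statistician compare conditions and try to relate events to it. This stands against a stronger reading that a reader might infer: that distress is analysed only through group means and could not appear in the results. The documents do not support that, since logged events can be reported and may be compared. What remains is that the comparison is conditional, distress is not defined as an event, and no final report by arm is planned.

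**The SAP's silence proves little.** SAP 1.0 says the plan "includes all plans for data summary and statistical analyses", but the sentence goes on to limit this to the study's hypotheses, and none of those in SAP 5.0 concerns safety. So the SAP cannot be read as claiming to hold every analysis, safety included. The gap has to be shown from both documents together, as above.

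**Supportive care visits are summarised by arm.** True, and distressed participants are referred to supportive oncology. But the visits are not specific to distress, an event in 1% to 2% of patients leaves the quartiles essentially unchanged, and the formal analysis pools the visits with admissions and emergency visits.

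**The risk is low.** The intervention is an information website, and the team reports no such distress in its earlier web-based work. This limits the weight of the point. It is also a claim that this trial could document at little cost.

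**Conclusion.** The point holds as a gap in planned reporting. No by-arm count of distress or adverse events is planned unconditionally, the mean comparisons in SAP 9.1 cannot show a rare, short-lived event, and the comparison in Protocol 17.0 could stay unused with a split as uneven as 8 v. 0.

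The dilution result rests on the assumed 0.5% to 2%, 1 to 2 SD and one month. It is not sensitive to them within reason: at 5% and 2 SD for one month, time-averaged power at alpha 0.01 is still 0.011, and single-month power is 0.16 if all cases coincide. The event counts are illustrations, not predictions. The under-1% figure is not an EC background rate.

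Nothing here suggests that EC causes distress, or that a table would settle the matter. It would make an imbalance visible and put an interval around it. Nor do the calculations support a threshold on Anxiety or Depression as the lead measure of harm.

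**What to change.** Add to SAP 9 a descriptive safety table, EC v. UC, in all randomised patients and not only the SAP 7.1 data set. That set drops anyone who gives no PRO after baseline, which could include a patient overwhelmed early. For each arm give the number and proportion with:

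1. a logged adverse event;
2. a distress referral or Crisis Protocol use.

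Report risk differences with 95% CIs, whether or not Protocol 17.0's trigger is met, labelled descriptive and outside the multiplicity adjustment. The distribution of individual worsening on Anxiety and Depression may be shown as support only.

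State the source of item 2. Protocol 16.0 provides for referral but does not say how referrals are recorded for analysis. The warehouse export for consented patients (Protocol 8.0) removes encounters with psychiatric providers, so a study log is the safer source.

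Cost: SAP wording and one table. SAP 1.0 says SAP changes need no protocol amendment. The drawbacks are small counts, wide intervals and possible ascertainment bias, since more contact with EC patients may bring more distress to light; the table's footnote should say so. No referral rule, alert threshold or other clinical procedure changes.
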